### Outcome measures

Primary outcome is diagnostic accuracy. Sensitivity, specificity and failure rates of MLPA are calculated for (an)euploidies 21, 13, 18, X and Y and compared with TKT as a reference test. Turnaround time on laboratory and patient level is recorded. Discordant test results and technical difficulties are counted, allowing for general and per centre analysis. The effect of a learning curve if present will be established.

#### Secondary outcomes

Quality of life questionnaires are filled out before amniocentesis and 2, 5, 14, 23 and 63 days after amniocentesis. The questionnaires contain Spielberger's State Trait and Anxiety Inventory (STAI), Impact of Event Scale (IES), Personal Perceived Control (PPC) and Medical Outcome Study Short Form (SF-36) and questions on background characteristics. We will compare two groups, one group, receiving the result of TKT and the other group, receiving results of both MLPA and TKT.

A discrete choice experiment will give insight in patient's preferences and investigates the value pregnant women place on different characteristics of prenatal testing (e.g. detection capacity, waiting time, consequences for the child of the detected abnormalities).

The process of care is distinguished into three cost categories; direct medical costs (all costs in the health care sector), direct non-medical costs (costs outside the health care sector that are affected by health status or health care) and indirect costs of the pregnant women and her partner. For each cost category, costs are measured as the volumes of resources used multiplied with appropriate valuations (cost-per-unit estimates, fees, national reference prices).

### Statistical issues

#### Sample size

Adopting the results of karyotyping as the gold standard and assuming that MLPA and karyotyping do not produce different test results, that not more than 1/500 missed cases of Down syndrome are accepted, and that the proportion of discordant test results is 0.002, we need at least 4500 paired test results to test the null-hypothesis of clinical equivalence (one-sided alpha 0.05, power = 1-beta = 0.90).

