#### Karyotyping

Karyotyping is a reliable and accurate test for detecting chromosomal aberrations. The karyotyping detection rate for Down syndrome is 99,5% [3].

The time from amniocentesis to diagnosis is 2–3 weeks, as the test is non-automated and samples need to be cultured in order to obtain foetal cells at the metaphase stage. Laboratory personnel involved in TKT are blinded for MLPA results. In case of an abnormal MLPA result and a more rapid test result is wanted, the earliest possible harvesting of cell cultures is carried out.

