#### Data analysis

Data will be analyzed according to both the intention to treat and per protocol analysis. To determine non-inferiority in diagnostic accuracy we will calculate absolute and relative sensitivity, specificity and failure numbers of MLPA and compare these to karyotyping (gold standard). Furthermore, the time cytogeneticists or molecular geneticists need to provide an authorized test results and the time needed to inform the patients is recorded. With these data exact waiting periods for both tests can be estimated.

Quality of life outcomes. Repeated measurement analysis will be performed for the between group evaluation.

Women's preferences. Responses on the discrete choice experiment will be analyzed using conditional logistic regression techniques.

Economic evaluation. Since the study is designed as an equivalence study, we hypothesize there is no difference in diagnostic accuracy between MLPA and TKT. The economic analysis is expected to be a cost-effectiveness analysis with maternal health as effectiveness.

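### The 1/500 margin and the 90% power apply to all 4500 women tested and do not carry over to sensitivity, on which the non-inferiority conclusion partly rests

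*Protocol article*

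**What the plan says.** The Sample size section takes karyotyping as the gold standard and lists its planning assumptions: "assuming that MLPA and karyotyping do not produce different test results", "not more than 1/500 missed cases of Down syndrome are accepted", and "the proportion of discordant test results is 0.002". From these it concludes "we need at least 4500 paired test results to test the null-hypothesis of clinical equivalence", with "one-sided alpha 0.05, power = 1-beta = 0.90". It does not say whether 1/500 is counted per woman tested or per affected fetus, and the article gives neither a prevalence nor an expected number of affected fetuses.

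The primary outcome is diagnostic accuracy. Under Outcome measures: "Sensitivity, specificity and failure rates of MLPA are calculated for (an)euploidies 21, 13, 18, X and Y", with karyotyping as the reference. Under Data analysis: "To determine non-inferiority in diagnostic accuracy we will calculate absolute and relative sensitivity, specificity and failure numbers of MLPA". Under Karyotyping, the reference test's own performance is given: "The karyotyping detection rate for Down syndrome is 99,5" per cent.

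**The concern.** Sensitivity is a proportion of affected fetuses. The sample size is a count of paired results in all women, most of whom will carry an unaffected fetus. A difference of 0.002 over all women is small on that scale, but it is a large fraction of a small number of affected fetuses. Data analysis nevertheless places sensitivity among the measures that decide non-inferiority, and the only margin and power in the article are those of the Sample size section.

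The study is meant to inform whether MLPA can replace karyotyping, and a missed trisomy is the main harm of replacement. If the whole-cohort criterion is met and reported as equivalent or non-inferior accuracy, readers will take it to cover sensitivity, which it does not.

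**Working it through.** **Inputs.** From Sample size: margin d = 1/500 = 0.002, discordance psi = 0.002, no net difference, one-sided alpha 0.05, power 0.90, N = 4500 pairs. From Karyotyping: detection rate 99.5%. Assumed, because the article gives none: 1%, 2% or 3% of women carry an affected fetus, that is 45, 90 or 135 cases. Cases and misses must refer to the same condition.

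**1. Where 4500 comes from.** Paired non-inferiority over all pairs:

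n = (1.645 + 1.282)^2 × 0.002 / 0.002^2 = 4282.

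Power at 4500: √4500 × 0.002 / √0.002 − 1.645 = 3.000 − 1.645 = 1.355, which gives 0.912.

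The stated 4500 is about 5% above 4282. Inflation by 1/0.95 would give 4508, but no such allowance is stated. The figure is consistent with rounding up on the all-women scale and is not treated here as an arithmetic error.

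**2. The margin expressed as sensitivity.** Per woman, 0.002 × 4500 = 9 missed cases. The share of cases lost is 0.002 / prevalence:

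| Assumed prevalence | Cases | True loss at the margin |
|---|---|---|
| 1% | 45 | 20% |
| 2% | 90 | 10% |
| 3% | 135 | 6.7% |

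Over a wider range, the loss is 40% at 0.5% prevalence and 4% at 5%.

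**3. What observed result would pass.** Nine is the true expectation at the null boundary, so it is not itself a passing result. If misses alone are counted, the one-sided 95% upper limit per woman is:

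| Misses in 4500 | Exact limit | Wald limit |
|---|---|---|
| 3 | 0.00172 | 0.00130 |
| 4 | 0.00203 | 0.00162 |
| 5 | 0.00234 | 0.00193 |
| 6 | 0.00263 | 0.00223 |

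Up to 3 misses pass on the exact bound and up to 5 on the Wald bound. As shares of cases these run from 3/135 = 2.2% to 5/45 = 11.1%.

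**4. If false positives offset misses.** With a net-difference Wald bound, 6 misses and no false positive fail (0.00223). Six misses with 2 false positives give (4 + 1.645 × √8) / 4500 = 0.00192 and pass. On that test, extra errors in the other direction can turn a failure into a pass, which says nothing favourable about sensitivity.

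**5. If 1/500 were meant per affected fetus.** With no miss, a one-sided 95% bound below 1/500 needs ln(0.05) / ln(0.998) = 1496.4, so 1497 affected fetuses. That is 1497/4500 = 33% of the cohort, or 49,900 to 149,700 women at 3% to 1% prevalence.

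**6. What 4500 women can show on sensitivity.** With no miss, the one-sided 95% lower limit is 0.05^(1/cases): 93.6% with 45 cases, 96.7% with 90 and 97.8% with 135.

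**The case against.** The strongest reply is that the Sample size section never claims power for sensitivity. It speaks of paired results, and on that scale its figure is sound. Sensitivity and specificity are already planned as primary measures, and 4500 pairs are ample for specificity and failure rate. All of this stands. The fault is that the non-inferiority conclusion takes in sensitivity while the only stated criterion belongs to another denominator.

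Three stronger readings are tempting, and the article does not support them.

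- A reader might infer that MLPA could be declared equivalent while losing 7% to 20% of Down syndrome cases. That is the true loss at the margin, under an assumed prevalence. With 9 misses truly expected and only misses counted, the study would pass about 12% of the time on a Wald bound and 2% on an exact bound.
- A reader might split the planned discordance evenly into 4.5 expected misses, turn that into a sensitivity of 90% to 96.7% for 45 to 135 cases, and say this passes about 90% of the time. The discordance is not limited to Down syndrome, so those misses and a Down syndrome case count need not match. The pass rate also needs false positives to offset misses, and the article names no test. Counting misses alone, it is about 70% (Wald) or 34% (exact).
- A reader might call the per-case reading a second failed design. That reading is unlikely: the unit is paired results, the all-pairs formula comes close to 4500, and a tolerance of 0.2% per case would be stricter than the 0.5% miss rate implied for karyotyping. What remains is an unstated denominator.

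Exact limits and a separate trisomy 21 result are details that an article may leave to a fuller document. Their absence is not the point.

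**Conclusion.** The concern holds in this limited form. The 0.002 margin and the 90% power were evidently set per woman tested and give no assurance about sensitivity. On an assumed 1% to 3% of women with an affected fetus, the margin corresponds to a true loss of 20% to 6.7% of cases. A result with 3 to 5 observed misses, about 2% to 11% of cases, would still meet the criterion if misses alone count, and more could pass if false positives offset them. Even a perfect result supports a lower limit for sensitivity of only 93.6% to 97.8%.

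These percentages depend on the assumed prevalence. The mismatch of denominators does not, and the per-case reading fails at any prevalence below about 33%. The margin also names Down syndrome alone, while the outcome covers chromosomes 21, 13, 18, X and Y. Pooling these adds cases, but reaching 1497 would take one affected fetus in every three women.

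**What to change.** Keep 4500 women.

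- In Sample size, state that 1/500 is per woman tested, and that the 90% power applies to whole-cohort discordance and not to sensitivity.
- In the same section, give the expected number of affected fetuses with the prevalence assumed, and the lower confidence limit for sensitivity that this number allows (for example 93.6% to 97.8% with 45 to 135 cases and no miss).
- In Data analysis, base any conclusion on sensitivity, for the target aneuploidies together and for trisomy 21 separately, on its exact confidence limit among affected fetuses. Do not claim equivalent or non-inferior sensitivity from the 1/500 criterion.

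The cost is rewording of two sections and no extra recruitment. The stated assurance becomes less favourable.

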## Background

In the Netherlands, invasive prenatal diagnosis is offered to all women who are considered to be at increased risk for Down's syndrome. Until recently, the vast majority of invasive tests was done for advanced maternal age. More recently, a nationwide screening program for Down's syndrome using first trimester serum testing combined with ultrasonographic nuchal translucency measurement was introduced [1,2]. A positive result of this combination test or maternal age (36 years or older) represent 80% of the indications for the invasive diagnostic procedures (amniocentesis and chorionic villus sampling). We have seen a still continuing shift of maternal age-based karyotyping towards prenatal screening based testing.

Traditional karyotyping (TKT) is considered the gold standard for invasive prenatal diagnosis (PND) [2,3]. TKT is able to detect a range of numerical and structural chromosomal abnormalities with considerable accuracy (99.4–99.8%) and reliability[3,4]. However, TKT also has several disadvantages: it is labour intensive and the costs are high. Furthermore, obtaining results from karyotyping takes 2–3 weeks, and this waiting time places a significant emotional burden on women and their partners[5]. Moreover, the extensive detection capacity of TKT can be perceived as a disadvantage due to the detection of abnormalities with unclear or mild clinical relevance. These results can cause patient anxiety, emotional dilemmas concerning the continuation of pregnancy and, albeit rare, unnecessary pregnancy terminations [6].

Due to these disadvantages, TKT has been challenged as a reference test. In 2002, a molecular PCR-based technique, MLPA (multiplex ligation-dependent probe amplification) became available to detect foetal aneuploidies in amniotic fluid cells. In preclinical laboratory studies, MLPA has been a robust test in detecting the most common chromosomal aneuploidies, namely trisomy 21, 13, 18 and sex chromosome abnormalities [7-9]. Compared to TKT, MLPA has several potential advantages: the result is available in 2–4 days instead of 3 weeks, the technique requires only 2 ml of amniotic fluid instead of 16–20 ml, and the technique is considerably less labour-intensive and is suitable for high-throughput testing [8-10].

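### The 4500 pairs and 90% power fit a net difference in which false positives offset misses, not the stated limit on missed cases; with an even split of the assumed discordance, exact power for that limit is about 34%

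*Protocol article*

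**What the plan says.** All the inputs stand in one sentence of the Protocol article, under Statistical issues, Sample size:

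- Reference and true difference: "Adopting the results of karyotyping as the gold standard and assuming that MLPA and karyotyping do not produce different test results".
- Acceptance limit: "that not more than 1/500 missed cases of Down syndrome are accepted".
- Disagreement between the tests, and the resulting size: "the proportion of discordant test results is 0.002, we need at least 4500 paired test results".
- Error rates: "one-sided alpha 0.05, power = 1-beta = 0.90".

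The sentence names no formula. It does not divide the discordance into misses and false positives, and it does not say what 1/500 is a fraction of.

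The Outcome measures section calculates sensitivity, specificity and failure rates for chromosomes 21, 13, 18, X and Y. The Data analysis section says that sensitivity and specificity, each compared with karyotyping, will be used to determine non-inferiority. Neither section names a formal test.

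**The concern.** The limit runs in one direction: it concerns cases that MLPA misses. Once karyotyping is the truth, every discordant pair is an MLPA error, either a miss or a false positive, and a false positive elsewhere in the cohort does not restore a missed trisomy. A calculation based on the difference between the two error types therefore describes a different question from the one the limit asks.

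The trial is meant to inform whether MLPA can replace karyotyping. If the 90% belongs to the net difference, it is not the chance of showing that misses are acceptably rare. A trial of 4500 pairs could then fall short on the stated criterion even when MLPA misses only half as many cases as the limit allows.

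**Working it through.** **Inputs (Sample size section).** Margin 1/500 = 0.002; discordance 0.002; true net difference 0; one-sided alpha 0.05 (z = 1.645); power 0.90 (z = 1.282); n = 4500.

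**Step 1: the plan's own figure.** Paired non-inferiority on (misses − false positives)/n with true difference 0:

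n = (1.645 + 1.282)² × 0.002 / 0.002² = 8.564 × 500 = 4282.

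Power at 4500 = Φ(0.002 × √(4500/0.002) − 1.645) = Φ(3.000 − 1.645) = 91%. Exact enumeration of the Wald version gives 90%. The 4282 is about 5% below 4500, which is compatible with rounding up.

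Other forms with the same inputs lie further away:

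| Form | Pairs |
|---|---|
| Net difference, two-sided 0.05 | 5254 |
| Net difference, two one-sided tests | 5411 |
| Net difference, restricted-likelihood score test | 5685 |
| Miss rate 0.002 against 0.001, one sample | about 12,994 |
| Zero misses allowed | 1497 |

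Adding a 5% loss to the first formula gives 4282/0.95 = about 4508, but the article states no such loss.

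**Step 2: the implied miss rate.** Discordance of 0.002 with zero net difference means misses = false positives = 0.001. In 4500 pairs that is 4.5 expected misses, against 9 at the limit.

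**Step 3: power for the written limit.** Read 1/500 as a fraction of all tests, and let X be the number of misses in 4500. Test H0: miss rate ≥ 0.002.

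| Passes if | True alpha, P(X ≤ c at 0.002) | Power at 0.001 |
|---|---|---|
| X ≤ 3 (exact) | 0.021 | 34% |
| X ≤ 4 (score/Wilson) | 0.055 | 53% |
| X ≤ 5 (Wald) | 0.115 | 70% |

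Only the first rule keeps the stated alpha of 0.05. To reach 90% at a miss rate of 0.001, the exact test needs about 12,750 pairs.

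**Step 4: dependence on the true miss rate (exact test, n = 4500).**

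| True miss rate | Power |
|---|---|
| 0.0015 | 10% |
| 0.001 | 34% |
| 0.0005 | 81% |
| 0.0004 | 89% |
| 0.0002 | 99% |

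**Step 5: dependence of the net-difference power on the split.** Discordance stays at 0.002, with exact enumeration of the Wald version:

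| Share of discordances that are misses | Probability of passing at 4500 |
|---|---|
| 50% | 90% |
| 60% | 77% |
| 75% | 47% |
| 100% | 11.5% |

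In the last row the miss rate equals the limit, so 11.5% is a false-acceptance rate against a nominal 5%.

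**The case against.** **The split and the test are inferred.** The article gives only total discordance. The even split follows from reading "assuming that MLPA and karyotyping do not produce different test results" as zero net difference, and the exact test is not named. This stands, and 34% must be quoted with those conditions. Looser rules give 53% to 70%, but they exceed the stated alpha and none reaches 90%.

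**A low miss rate alone gives high power.** A reader might infer that 90% power is available only if false positives cancel misses. That is not so: without any netting, the exact test has 89% power at a miss rate of 0.0004 and 99% at 0.0002.

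**The event sets may differ.** The limit names Down syndrome, while the primary outcome covers five chromosomes. If the 0.002 covers all of them, misses of Down syndrome are fewer than assumed here and power against 1/500 is higher. This also stands, and the article does not settle it.

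**The denominator is open.** If 1/500 is a fraction of Down syndrome cases, neither the 90% nor the 34% applies. That reading does not rescue the calculation: excluding 1/500 at one-sided 0.05 would take about 1497 affected pregnancies with no miss, a third of the 4500.

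**No netted test is planned.** A reader might infer that the trial will pass MLPA by setting false positives against misses. The Data analysis section treats sensitivity and specificity as separate measures and adopts no netted test. The criticism therefore applies to the sample size justification and does not show that the analysis is wrong.

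**Karyotyping error.** A reader might also argue from the karyotyping accuracy in the Background that 0.002 is too low. That figure covers a range of numerical and structural abnormalities beyond the target aneuploidies, and the argument conflicts with "Adopting the results of karyotyping as the gold standard". It forms no part of this point.

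**Conclusion.** The point holds in a conditional form. The stated size and power are approximately recovered from a net-difference calculation and from no other form tried, while the stated limit is on misses alone. If 1/500 is a fraction of all tests, the discordance splits evenly, and all assumed misses count against the limit, power at 4500 is about 34% for a test that respects alpha 0.05. The stated 90% for the written criterion needs a true miss rate of just under 0.0004, about a fifth of the assumed discordance. The documents do not show that MLPA's miss rate is as high as 0.001, so 34% is what the plan's own assumptions imply under this reading and is not a forecast. Even on its own terms, the net-difference power depends on an even split that the article never states.

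**What to change.** 1. State the denominator of 1/500 (all tests or affected cases) and the event set it covers (Down syndrome or all target chromosomes).
2. Make the primary non-inferiority test an exact one-sided 95% upper limit for the missed-case rate, compared with 1/500. If the denominator is all tests and n = 4500, this passes at 3 misses or fewer.
3. Report a separate exact limit for the false-positive rate.
4. Replace the single 90% figure with the power of that test at 4500 over a range of true miss rates: 34% at 1/1000, 81% at 1/2000 and 99% at 1/5000. These figures assume the all-tests denominator and must be recalculated if item 1 settles on another.

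The cost is a few sentences in the Sample size and Data analysis sections and one exact interval for each error type. No extra enrolment or data collection is needed. The drawback is a less favourable stated power.

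### With about 9 discordant pairs expected, a test that truly holds one-sided 5% has at most about 86% power at 4500 pairs on the natural paired-difference reading, not 90%

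*Protocol article*

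**What the plan says.** The Sample size section treats karyotyping as the gold standard and plans "assuming that MLPA and karyotyping do not produce different test results". It sets the limit as "not more than 1/500 missed cases of Down syndrome are accepted" and assumes that "the proportion of discordant test results is 0.002". From these inputs it concludes: "we need at least 4500 paired test results to test the null-hypothesis of clinical equivalence (one-sided alpha 0.05, power = 1-beta = 0.90". It names no formula and no test.

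The Data analysis section sets the framework, also without naming a test: "To determine non-inferiority in diagnostic accuracy we will calculate absolute and relative sensitivity, specificity and failure numbers of MLPA".

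**The concern.** Large-sample formulas for paired proportions depend on the number of discordant pairs, not on the number of women. Here 4500 x 0.002 = 9 discordant pairs are expected in total. With so few, a normal-approximation test can have a true error rate well away from its nominal one, and a test corrected for this loses power. The printed pair of figures, 5% error and 90% power, may then not be attainable together.

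The type I error is the chance of declaring MLPA non-inferior when it in fact sits at the unacceptable limit. The study is meant to inform whether MLPA can replace karyotyping, so this error rate matters most. An analyst who picks the test that matches the sample-size formula could exceed the stated 5% without noticing. One who picks a test that holds 5% would have less power than the protocol states.

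**Working it through.** **Notation.** p10 is the proportion of pairs that karyotyping calls abnormal and MLPA does not (misses). p01 is the proportion with the reverse discordance.

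**Inputs from the Sample size section.** N = 4500; one-sided alpha 0.05; power 0.90; limit 1/500 = 0.002; discordant proportion 0.002; no true difference.

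**Assumptions needed to make these testable (mine).**
- The limit is a margin on p10 - p01 over all pairs.
- Under the alternative p10 = p01 = 0.001, so 4.5 discordances are expected in each direction.
- Under the null p10 - p01 = 0.002 with p01 free, and the error must be at most 5% at every p01.

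**Step 1: reproduce the plan's figure.**
n = (z.95 + z.90)^2 x discordance / margin^2 = (1.645 + 1.282)^2 x 0.002 / 0.002^2 = 4282 (unrounded quantiles).
At 4500 pairs, margin / SE = 0.002 / sqrt(0.002/4500) = sqrt(9) = 3, so the approximate power is Phi(3 - 1.645) = 91.2%. The stated figure is consistent with 4282 rounded up.

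**Step 2: true size of the Wald test that goes with this formula.** It declares non-inferiority when b - c + 1.645 x sqrt(b + c) is below 4500 x 0.002 = 9, where b is the number of misses and c the number of reverse discordances (a negligible variance term is omitted). With c = 0:
- b = 5: 5 + 1.645 x 2.236 = 8.68, below 9, so it passes.
- b = 6: 6 + 1.645 x 2.449 = 10.03, above 9, so it fails.

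At the null point p10 = 0.002, p01 = 0, misses follow Bin(4500, 0.002) with mean 9, and P(b <= 5) = 11.54%. Full trinomial enumeration along the null boundary gives:

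| p01 under the null | true size of the Wald test |
|---|---|
| 0 | 11.54% |
| 0.0005 | 7.5% |
| 0.001 | 6.9% |
| 0.002 | 5.9% |
| 0.003 | 5.3% |

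Its exact power at p10 = p01 = 0.001 is 90.4%.

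**Step 3: tests that hold, or nearly hold, 5% at 4500 pairs.**

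| test | power | maximum true size |
|---|---|---|
| Wald | 90.4% | 11.5% |
| restricted-likelihood score, asymptotic cut-off | 85.3% | 5.5% |
| exact unconditional, score ordering | 82.9% | 4.7% |

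**Step 4: ceiling over all tests.** By the Neyman-Pearson lemma, the single null point p10 = 0.0025, p01 = 0.0005 already caps the power of any 5% test at 86.1%. Linear programming over all tests, randomised ones included, with size at most 5% along the null boundary, gives 86.0%. Allowing a true size of 7% lifts the ceiling to 89.8%, and 7.5% lifts it to 90.5%.

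**Step 5: pairs needed for 90% at a true 5%.** The best conceivable test needs about 5150. The exact score-ordered test first reaches 90% at 5400 (searched in steps of 100; power 90.5%).

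**Step 6: the reading with karyotyping as an error-free reference.** If the limit is put on the miss proportion itself, the one-sided 95% exact upper limit is 0.172% for 3 misses in 4500 and 0.203% for 4, so at most 3 misses are allowed. With 4500 x 0.001 = 4.5 expected misses, P(at most 3) = 34%. The power figures of Step 3 do not apply to that rule.

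**The case against.** **The number is not a miscalculation.** A reader might infer an arithmetic error. The documents do not support that: the stated inputs give 4282 by the conventional formula, and the text asks for at least 4500. The weakness is relying on the approximation at 9 events. This stands.

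**The 11.5% is a corner case.** A reader might infer that the trial runs more than double its stated error, or that 90% power is reachable only with a Wald test. Neither holds. The 11.5% needs every discordance under the null to be a miss; with some reverse discordances the Wald size is 5% to 7.5%. A score statistic with a looser cut-off (-1.456) also reaches 90.2% power, at 7.4% true size. And no test is named, so nothing shows that a Wald test will be used.

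**The ceiling depends on assumptions that the text does not fix.**
- If discordance is held at exactly 0.002 under the null too (p10 = 0.002, p01 = 0), declaring non-inferiority whenever any reverse discordance appears has zero error, and power 1 - 0.999^4500 = 98.9%.
- If no difference means no discordance at all, power is 100%.
- If the split favours MLPA (p10 = 0.00075), the score test has 96.6% power.

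So a claim that no 5% test can work on any reading would be wrong. These readings are strained, however. The first treats a planning guess as known fact, the second conflicts with the discordance of 0.002 in the same sentence, and the third conflicts with the assumption of no difference.

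**The choice of test may sit in the full protocol or SAP.** True, and the missing name is not the complaint. The ceiling covers every test, so on the stated assumptions no later choice makes the two printed figures hold together.

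**Conclusion.** The point holds on the natural reading: a margin of 0.002 on the paired difference, an even split of the 0.002 discordance under the alternative, and error controlled whatever the null discordance. On it, 4500 pairs give at most about 86% power to any test with true one-sided size of 5% or less, and 83% to 85% to the tests one would actually use (the 85.3% comes with size up to 5.5%). The stated 90% can be had only by accepting a true error somewhat above 7%. With the Wald test that matches the formula, the error is about 7% to 7.5% at p01 of 0.0005 to 0.001, and at worst 11.5%. The shortfall is thus about 4 to 7 percentage points of power, or an unacknowledged inflation of the error rate. It does not show that the sample size was miscalculated or that the trial's actual error will exceed 5%.

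**What to change.** In the Data analysis section, name the primary non-inferiority test for the paired comparison. Either:
- an exact unconditional matched-pair test with score ordering (about 83% power, size 4.7%); or
- the restricted-likelihood score test, disclosing that its true size can reach 5.5% (85.3% power).

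In the Sample size section, restate the power at 4500 pairs as about 83% to 85%, according to the test chosen. Say there that 1/500 is a margin on the paired difference and that the 0.002 discordance is taken as evenly split.

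Do not attach this power to a rule of at most 3 misses in 4500. If the analysis treats karyotyping as error-free and tests the miss proportion directly, that rule passes only about 34% of the time with 4.5 expected misses, and the power must be stated separately.

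The cost is one sentence in each section and a less favourable power statement. No extra women are needed; about 5400 pairs would be required only if 90% power with the exact test were to be kept.

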## Methods/Design

### Aims

The M.A.K.E. study investigates whether MLPA can replace TKT in prenatal diagnosis in terms of diagnostic accuracy, costs and maternal quality of life for women undergoing amniocentesis for the indications advanced maternal age and increased risk following prenatal screening.

We hypothesize that MLPA has equivalent diagnostic accuracy in detecting trisomies 21, 18, 13 and sex chromosome abnormalities. The reduction in waiting time for the patient, maternal quality of life, women's preferences, the relevance of 'unexpected findings' and costs are part of the study.

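### The primary hypothesis is written in reverse, with equivalence as the null, and the stated aim moves between equivalence and non-inferiority; the 90% power fits only one-sided non-inferiority

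*Protocol article*

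**What the plan says.** The Sample size section gives the number of pairs needed "to test the null-hypothesis of clinical equivalence (one-sided alpha 0.05, power = 1-beta = 0.90". Its other inputs are that MLPA and karyotyping are assumed not to differ, that "not more than 1/500 missed cases of Down syndrome are accepted", and that "the proportion of discordant test results is 0.002".

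The aim is named in several places, not consistently:

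- **Aims:** "We hypothesize that MLPA has equivalent diagnostic accuracy".
- **Sample size:** clinical equivalence, as the null.
- **Data analysis, diagnostic accuracy:** "To determine non-inferiority in diagnostic accuracy we will calculate absolute and relative sensitivity".
- **Data analysis, economic evaluation:** "Since the study is designed as an equivalence study".
- **Discussion:** the purpose is given as evidence of clinical equivalency.

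The Data analysis section lists the quantities to be calculated. It does not tie a confidence limit or a decision rule to the 1/500 limit.

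**The concern.** A test protects against wrongly rejecting its null. If the null is equivalence, the 5% alpha limits the chance of wrongly rejecting a good test. The chance of wrongly accepting a worse one becomes a type II error. That error is planned at 10%, and it grows if fewer pairs are obtained. For a study meant to decide whether MLPA can replace karyotyping, the 5% protection should be on the other side.

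The shift in aim raises a second problem. Non-inferiority is a one-sided claim. Equivalence is two-sided and needs a larger sample for the same power. One power figure cannot serve both on the same inputs.

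**Working it through.** **Inputs, all from the Sample size section.** One-sided alpha 0.05; power 0.90; limit m = 1/500 = 0.002; discordant proportion p = 0.002; true difference 0; N at least 4500. I read 1/500 as a share of all paired results, which the article does not spell out.

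**1. The plan's own figure.** The article gives no formula. The usual one for a paired one-sided non-inferiority test with no true difference is

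n = (z₀.₉₅ + z₀.₉₀)² × p / m²

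= (1.64485 + 1.28155)² × 0.002 / 0.002² = 8.5638 × 500 = 4281.9, so 4282 pairs.

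This is 4.8% below 4500, which the text gives as a minimum. At 4500 pairs, the margin in standard errors is √(4500 × 0.002² / 0.002) = √9 = 3, so power = Φ(3 − 1.645) = 0.912. A simulation with Wald limits gave 0.904. The stated 90% is reproduced for this aim.

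**2. The same inputs for equivalence.** For two one-sided tests within ±0.002 at alpha 0.05 each, z₀.₉₀ is replaced by z₀.₉₅:

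n = (1.64485 + 1.64485)² × 500 = 5411.1, so 5412 pairs.

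Power at 4500 = 2 × 0.912 − 1 = 0.82 (simulated 0.81).

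**3. Can the direction of the null change the conclusion?** Take 8 misses and 4 false positives in 4500 pairs, which is 12 discordances against the 0.002 × 4500 = 9 planned.

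- *Stated null.* The one-sided McNemar test gives z = (8 − 4)/√12 = 1.155, p = 0.12. The exact version gives P(X ≥ 8 | 12, ½) = 794/4096 = 0.19. Both keep equivalence.
- *Correct null.* Difference = 4/4500 = 0.00089. Standard error = √(12 − 16/4500)/4500 = 0.00077. The one-sided 95% upper limit = 0.00089 + 1.645 × 0.00077 = 0.00215. This exceeds 0.002, so non-inferiority is not shown.

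**4. Dependence on the number of pairs.** Suppose the true excess of misses is exactly 0.002, with all discordance in that direction. At 4500 pairs, a test of the stated null is non-significant in 0.6% (asymptotic) to 5.5% (exact) of simulated trials. With 1000 pairs, the exact test is non-significant in about 95%. A test of the correct null does not reward a small sample in this way.

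**The case against.** The strongest reply is that only the wording slipped. An acceptance limit, no assumed difference and a one-sided alpha are non-inferiority inputs, the Data analysis section names non-inferiority for the accuracy comparison, and the 90% power is reproduced on that reading. This stands as regards the arithmetic. It does not remove the problem, because the sentence at issue states the primary hypothesis and nothing else in the article corrects it.

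A reader might infer that the plan will declare equivalence whenever a difference is not significant. The article states no such rule, and a condensed article may leave the decision rule to the full protocol or analysis plan. The inference goes beyond the text. It also does not follow that a claim of equivalence would be nearly guaranteed. At 4500 pairs, a true deficit at the limit would usually be detected in the scenario of step 4. With exactly the planned 9 discordances and the normal approximation, the two approaches agree on every split against MLPA: 5–4 and 6–3 pass both (upper limits 0.00132 and 0.00176), while 7–2, 8–1 and 9–0 fail both (0.00221, 0.00265 and 0.00310). The disagreement is real but arises in particular data patterns.

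A reader might also infer that the study is underpowered. It is not, for the one-sided design that its inputs describe. The 82% applies only if the two-sided equivalence claim is kept, and the article nowhere mentions a two-sided margin. What stands is that equivalence is the aim named in the Aims, the Sample size section, the economic evaluation and the Discussion.

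**Conclusion.** The null hypothesis is stated in the wrong direction, and the aim is not the same throughout. Both are errors in the text as it stands and should be fixed. The planned number of pairs is not at fault: 4500 gives about 91% power for one-sided non-inferiority, and about 82% for equivalence within ±0.002. The direction of the null can change the conclusion, as 8 misses against 4 false positives shows.

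These figures rest on 1/500 being a share of all pairs, on the normal approximation, and on a reconstructed formula. If the limit was meant as a share of Down syndrome cases, the calculations above do not apply.

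**What to change.** - In the Sample size section, state H0 as MLPA worse than karyotyping by 0.002 or more, and H1 as worse by less than 0.002.
- In the Data analysis section, conclude non-inferiority only if the one-sided 95% upper limit of the paired difference is below 0.002. Name the interval method. With so few discordances a simple Wald limit is liberal: at a true excess of 0.002, all in one direction, it passed in 11.6% of simulated trials of 4500 pairs. A score-type limit is the safer choice.
- Use non-inferiority in the Aims, Sample size, Data analysis (including the economic evaluation) and Discussion.
- If an equivalence claim is kept, specify two one-sided tests and restate the power at 4500 pairs as about 82%, or plan about 5412 pairs for 90% by the same formula.

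Under non-inferiority the cost is a change of wording: the term equivalence is given up, and the sample size, margin, alpha and stated power stay as they are.
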